**Protocol S1**

**Effect of Modest Caloric Restriction on Oxidative Stress in Women, a Randomized Trial.**

It is not established to what extent caloric intake must be reduced to lower oxidative stress in humans. The aim of this study was to determine the effect of short-term, moderate caloric restriction on markers of oxidative stress in overweight and obese premenopausal women. We will conduct a randomized trial in women assign to one of two groups. One group will serve as a control group. This group will be given food containing 100% of daily caloric requirements. The second experimental group will be given a diet containing 75% of daily caloric requirements. This study is trying to determine how a low calorie diet might affect oxidative stress humans.

**Study site location and design:**

This randomized trial will be conducted at Vanderbilt University Medical Center. Eligible participants are premenopausal overweight and obese women, with inclusion criteria of: BMI more than25 kg/m^2^ and willingness to abstain from alcohol consumption for the duration of the study, complete an overnight stay in the Clinical Research Center (CRC), and come to the CRC daily to obtain study foods.

**Experimental Design:**

This study will consist of a 4 (28 days) dietary study, and 4 follow up visits (at week 2 and months 3, 6, and 12 after the dietary study).

Below is a chart of all the tests and when they will be performed.

| **Days** | **Screening 1** | **Screening 2** | **0** |
| --- | --- | --- | --- |
| Metabolic room / Cart | X |  |  |
| Weight | X | X | X |
| Height/waist/hips |  | X | X |
| Body Composition |  | X |  |
| Blood |  | X | X |
| 24Hr.Urine |  | X | X |
| Food Diary | X | X | X |
| Physical activity | X |  | X |

| **Days** | **1** | **2** | **3** | **4** | **5** | **6** | **7** | **8** | **9** | **10** | **11** | **12** | **13** | **14** |
| --- | --- | --- | --- | --- | --- | --- | --- | --- | --- | --- | --- | --- | --- | --- |
| Metabolic room / Cart |  |  |  |  |  |  |  |  |  |  |  |  |  | X |
| Weight | X | X | X | X | X | X | X | X | X | X | X | X | X | X |
| Height/waist/hips | X | X | X | X | X | X | X | X | X | X | X | X | X | X |
| Body Composition |  |  |  |  |  |  |  |  |  |  |  |  |  |  |
| Blood |  |  | X |  | X |  | X |  |  |  |  |  |  | X |
| 24Hr. Urine collection |  |  | X |  | X |  |  |  |  | X |  |  |  | X |
| Food Diary | X | X | X | X | X | X | X | X | X | X | X | X | X | X |
| Physical activity | X | X | X | X | X | X | X | X | X | X | X | X | X | X |

| Days | 15 | 16 | 17 | | 18 | 19 | 20 | | 21 | 22 | 23 | | 24 | 25 | 26 | | 27 | 28 | 29 |
| --- | --- | --- | --- | --- | --- | --- | --- | --- | --- | --- | --- | --- | --- | --- | --- | --- | --- | --- | --- |
| Metabolic room or cart |  |  |  | |  |  |  | |  |  |  | |  |  |  | |  | X |  |
| Fat Biopsy |  |  |  | |  |  |  | |  |  |  | |  |  |  | |  |  |  |
| Weight | X | X | X | | X | X | X | | X | X | X | | X | X | X | | X | X | X |
| Height/waist/hips | X | X | X | | X | X | X | | X | X | X | | X | X | X | | X |  | X |
| Body Composition | X |  |  | |  |  |  | |  |  |  | |  |  |  | |  |  | X |
| Blood |  |  |  | |  |  |  | | X |  |  | |  |  |  | |  |  | X |
| 24Hr. Urine collection |  |  | X | |  |  | X | |  | X |  | |  | X |  | | X |  | X |
| Food Diary | X | X | X | | X | X | X | | X | X | X | | X | X | X | | X | X | X |
| Physical activity | X | X | X | | X | X | X | | X | X | X | | X | X | X | | X | X | X |
| **Follow-up Period** | **2 week** | | | **3-months** | | | | **6-months** | | | | **12-months** | | | |  |  |  |  |
| Metabolic room /Cart | X | | | X | | | | X | | | | X | | | |  |  |  |  |
| Weight | X | | | X | | | | X | | | | X | | | |  |  |  |  |
| Height/waist/hips | X | | | X | | | | X | | | | X | | | |  |  |  |  |
| Body Composition | X | | | X | | | | X | | | | X | | | |  |  |  |  |
| Blood | X | | | X | | | | X | | | | X | | | |  |  |  |  |

**Weight, height, waist and hip circumference measurements:**

Body weight will be measured with a calibrated scale and height measured with a wall-mounted height meter while in street clothes with no outerwear or shoes.

**Blood Analysis:**

Pregnancy test, catecholamines, insulin, leptin, isoprostanes, carnitine, c-reactive protein, interleukin, and genetic screening. The amounts will be as follows:

| Days | -7 | 0 | 3 | 5 | 7 | 14 | 21 | 28 | 35 |
| --- | --- | --- | --- | --- | --- | --- | --- | --- | --- |
| Amount* Drawn | 42ml | 25ml | 5 ml | 5 ml | 25 ml | 30 ml | 25 ml | 30 ml | 25 ml |

| Follow-up Days | 2 weeks | 3 months | 6 months | 12 months | Total  Entire Study |
| --- | --- | --- | --- | --- | --- |
| Amount* Drawn | 32 ml | 32 ml | 32 ml | 32 ml | 315 ml (< 1 cup) |

*1 tablespoon = 15 ml; 1 teaspoon = 5 ml

**Urine Analysis:**

Collect 24-hour urines during one weekdays and one weekend day of each study period for a total of eight (10) 24-hour urine collections.

**Statistical analysis**

Daily caloric intake and resting energy expenditure are expressed as the absolute and deficit number of kilocalories per day. The baseline characteristics between treatment and control groups are compared using the non-parametric Wilcox test. The effect of energy restriction on F_2_-isoprostane was evaluated using a paired t-test on the pre- and post-diet measurements. The effects of adiposity on F_2_-isoprostane concentration at different time points were determined by a multivariate analysis of variance with repeated measures in which body fat was treated as the independent variable. Residual analysis was performed for evaluation of model adequacy and outliers. A P-value < 0.05 was used for inclusion of terms in the regression and to indicate statistical significance. Analyses were performed with STATA 11 (StataCorp, College Station, TX) and R ([www.r-project.org](http://www.r-project.org/)) and all summary statistics are presented as means ± SD.

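### The protocol tests baseline balance by P-value and fixes no baseline covariate for comparing the arms; a prespecified ANCOVA of 75% against 100% would be the better use of data already collected

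*Protocol*

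**What the plan says.** The opening section of the Protocol sets out a randomised design: "We will conduct a randomized trial in women assign to one of two groups", one given 100% and the other 75% of daily caloric requirements.

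The Statistical analysis section then makes four relevant statements.

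- Baseline: "The baseline characteristics between treatment and control groups are compared using the non-parametric Wilcox test". It does not say which characteristics, how many, or what follows from the result.
- Diet effect: "The effect of energy restriction on F_2_-isoprostane was evaluated using a paired t-test on the pre- and post-diet measurements". No arm term or covariate is mentioned.
- Adiposity: a "multivariate analysis of variance with repeated measures in which body fat was treated as the independent variable". This concerns body fat, not the diet contrast, and the time at which body fat is measured is not stated.
- Threshold: "A P-value < 0.05 was used for inclusion of terms in the regression and to indicate statistical significance". The regression is not described further.

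The chart under Experimental Design schedules blood on day 0 and body composition at Screening 2. The Blood Analysis section lists isoprostanes among the analytes.

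**The concern.** If randomisation is sound, any baseline difference between the arms arose by chance. The null hypothesis of the baseline test is then true by design. Whether an imbalance distorts an arm comparison depends on its size and on how strongly the variable predicts the outcome. A Wilcoxon P-value measures neither: it can miss an imbalance that matters and flag one that does not.

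The useful response to chance imbalance is to choose prognostic baseline variables beforehand and adjust for them. The section does not do this. Its only stated rule for covariates is inclusion at P < 0.05, under which a prognostic variable can drop out of the model because of the data in hand. Its use of baseline F2-isoprostane is confined to subtraction in a paired test.

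At stake are the precision of the randomised comparison of 75% with 100%, and its protection against chance imbalance, in a trial that already collects the values needed.

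**Working it through.** The protocol states no sample size, SD, effect size or correlation, so there is no figure of its own to reproduce. Everything below is illustration under stated assumptions.

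**1. What the baseline test can and cannot detect**

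The observed difference needed for P < 0.05 (normal approximation) is about 1.96 × √(2/n) SD, with n women per arm (assumed):

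| n per arm | Difference needed |
| --- | --- |
| 10 | 0.88 SD |
| 20 | 0.62 SD |
| 30 | 0.51 SD |
| 50 | 0.39 SD |

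An observed imbalance of 0.5 SD would therefore usually pass unflagged at 20 per arm and usually be flagged at 50, although its effect on an unadjusted arm comparison is the same.

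Conversely, with k independent characteristics each tested at 0.05, the chance of at least one significant difference under perfect randomisation is 1 − 0.95^k: 23% (k = 5), 40% (k = 10), 54% (k = 15). The number of tests is not stated. Weight, waist, hips and body composition are likely to be correlated, which would lower these figures.

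**2. What a chance imbalance does to each kind of analysis**

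Let D be the chance difference between arms in baseline F2-isoprostane, in SD units, and r the correlation of baseline with post-diet value, with equal SDs at both times. The error left in the estimate is:

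- post-only arm comparison: r × D
- change-score arm comparison: −(1 − r) × D
- ANCOVA on baseline: 0 (linear relation assumed)
- pre/post paired test: none from this source, because it has no arm contrast

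With D = 0.5 and r = 0.6:

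- post-only: 0.6 × 0.5 = +0.3 SD
- change score: −(1 − 0.6) × 0.5 = −0.2 SD

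D = 0.5 is a sizeable imbalance. Its standard error is √(2/n), or √(2/20) = 0.32 SD at 20 per arm. There 0.5 is 0.5/0.316 = 1.58 standard errors, reached in one direction or the other in about 11% of trials.

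**3. Precision**

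With SD 1 at both times, the variance per woman is 1 for the post-only value, 2(1 − r) for the change and 1 − r² for ANCOVA. Hence:

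- ANCOVA relative to post-only: 1 − r²
- ANCOVA relative to change score: (1 − r²) / [2(1 − r)] = (1 + r)/2

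| r (assumed) | vs change score | vs post-only |
| --- | --- | --- |
| 0.3 | 0.65 | 0.91 |
| 0.5 | 0.75 | 0.75 |
| 0.6 | 0.80 | 0.64 |
| 0.7 | 0.85 | 0.51 |

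Over this range ANCOVA has the smaller variance against either alternative. The figures cover adjustment for baseline F2-isoprostane only. The further gain from body fat cannot be sized from the document.

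**The case against.** The strongest reply is that the baseline test alters no estimate. The protocol says only that the characteristics are compared. It does not say that the result decides comparability, selects covariates or triggers any action. This stands: removing those P-values is a reporting change with no gain in the estimate.

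A reader might infer that baseline values play no part in the analysis. The document does not support that. The paired test subtracts each woman's own pre-diet value, body fat enters a separate model, and the undescribed regression could contain baseline terms. Differencing is nevertheless not covariate adjustment: a between-arm comparison of changes would still carry the −0.2 SD shift shown above.

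A reader might also infer that a chance imbalance biases the diet effect as now planned. It does not. The stated test is within-person, and the shifts of +0.3 and −0.2 SD belong to arm comparisons that the section does not contain.

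Finally, covariates are commonly left to a statistical analysis plan, which is not at hand. Silence on covariates alone would be no finding. What can be faulted is what the protocol does state: a paired test for the diet effect, term inclusion by P-value, and a significance test of baseline balance. The choice of body fat as a second covariate is partly a matter of judgement, though the protocol itself models F2-isoprostane on it.

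**Conclusion.** The point holds as a low-cost improvement of method. The baseline Wilcoxon test is uninformative under sound randomisation, P-based inclusion of terms is a poor covariate rule, and no baseline covariate is fixed for an arm comparison. A prespecified ANCOVA would be better than the stated paired test.

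Under assumed correlations of 0.3 to 0.7, the gain is a variance 15% to 35% below that of an unadjusted change-score contrast, and 9% to 49% below that of a post-only contrast. It also removes the shift that a chance baseline imbalance would leave in either. These figures assume equal SDs before and after the diet and a linear relation; none comes from the trial's own data.

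The larger weakness in the same section is that the diet effect is stated without a contrast between the randomised arms. Adjustment has no purpose until that contrast is written in, so the two changes belong together.

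**What to change.** In the Statistical analysis section, replace the paired t-test as the analysis of the diet effect with wording such as:

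> The effect of energy restriction is the difference between the 75% and 100% arms in post-diet F2-isoprostane, estimated by ANCOVA with day 0 F2-isoprostane and Screening 2 body fat as covariates. Both covariates are fixed in advance and kept whatever their P-value or observed imbalance.

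Confine the P < 0.05 inclusion rule to exploratory models, or remove it. Replace the Wilcoxon sentence by a statement that baseline characteristics are described by arm without P-values.

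Name the day of the post-diet sample when doing this: the chart of tests shows blood on day 29, the blood volume table shows day 28, and the two must be reconciled.

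The cost is one or two degrees of freedom. No new visits or samples are needed, since blood on day 0 and body composition at Screening 2 are already scheduled. It is more than an editorial change, because the stated main analysis becomes a between-arm comparison.

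### The effect of caloric restriction is tested by a within-person pre/post comparison, so the randomised control group plays no part in the answer

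*Protocol*

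**What the plan says.** The protocol's opening section sets up a parallel-group comparison: "We will conduct a randomized trial in women assign to one of two groups". It continues: "One group will serve as a control group". Of the control group it says "This group will be given food containing 100% of daily caloric requirements", and of the other, "The second experimental group will be given a diet containing 75% of daily caloric requirements". The aim is the effect of moderate caloric restriction on markers of oxidative stress.

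The Statistical analysis section names one test of that effect: "The effect of energy restriction on F_2_-isoprostane was evaluated using a paired t-test on the pre- and post-diet measurements". It does not say whether the test is run in the restricted arm, in each arm or in both arms pooled.

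Two other analyses are described there:

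- A comparison of the arms before treatment: "The baseline characteristics between treatment and control groups are compared using the non-parametric Wilcox test".
- A repeated-measures multivariate analysis of variance for adiposity, with body fat as the independent variable. Randomised arm is not named in it.

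No between-arm comparison of post-diet F2-isoprostane or of its change is stated, and no arm-by-time term.

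**The concern.** A control group is there to show what would have happened to F2-isoprostane without the 25% restriction. The paired test does not use that information. It estimates the total change over the diet period, which is the restriction effect plus everything else that changed between the two samples.

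The protocol itself gives both arms common exposures. Both receive supplied food. Study site location and design requires daily visits to the research centre and "willingness to abstain from alcohol consumption for the duration of the study" of every participant. Assay drift or chance variation in the baseline value could add to this. If such factors lower F2-isoprostane equally in both arms, the paired test can still be significant, and the protocol's wording would attribute the result to energy restriction.

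Running the test separately in each arm does not help. Finding significance in the restricted arm and none in the control arm is not a test that the arms differ.

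F2-isoprostane is the only oxidative-stress marker given a test of the diet effect, so this sentence carries the answer to the trial's aim.

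**Working it through.** **Structure.** The paired sentence can be read in three ways. Write Δ for the restriction effect and s for the change shared by both arms.

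| Where the paired test is run | What it estimates | Compares 75% with 100%? |
|---|---|---|
| Restricted arm only | s + Δ | No |
| Each arm separately | s + Δ and s, each against zero | No |
| Both arms pooled (equal size) | s + Δ/2 | No |
| *Between-arm difference in change (not in the plan)* | (s + Δ) − s = Δ | Yes |

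Only the last row isolates Δ, and the protocol does not contain it. The defect follows from this alone, without any calculation.

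**Illustration of size.** The protocol states no sample size, SD or effect size, so there is no figure to reproduce. Inputs:

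- Significance level 0.05, from the Statistical analysis section; two-sided is assumed.
- n = 10, 20 and 40 women per arm, assumed.
- Δ = 0, so every significant result is a false positive for restriction.
- Shared shift d, in SDs of the within-person change: 0, 0.1, 0.3 and 0.5, assumed.

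The paired t statistic has a noncentral t distribution with n − 1 degrees of freedom and noncentrality d√n. The rejection probability is P(|t| > t₀.₉₇₅,ₙ₋₁). For example, with n = 20 and d = 0.5 the noncentrality is 0.5 × √20 = 2.236, the critical value is 2.093 and the probability is 56.5%.

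| Shared shift d | n = 10 | n = 20 | n = 40 |
|---|---|---|---|
| 0 | 5.0% | 5.0% | 5.0% |
| 0.1 | 5.9% | 7.1% | 9.5% |
| 0.3 | 13.6% | 24.7% | 45.7% |
| 0.5 | 29.3% | 56.5% | 86.9% |

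Pooling the arms doubles n, so a pooled test with 20 per arm has the n = 40 figures.

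**One arm significant, the other not.** With independent arms and equal rejection probability p, the restricted arm alone is significant with probability p(1 − p). With 20 per arm:

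- d = 0.3: 0.247 × 0.753 = 18.6%.
- d = 0.5: 0.565 × 0.435 = 24.6%.

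**Between-arm test under the same conditions.** In 40,000 simulated trials per setting (n = 10, 20 and 30 per arm; shared shift 0 to 1 SD), a two-sample t-test on change rejected in 4.8% to 5.1%.

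**Choice of between-arm method.** In units of the outcome variance, with pre/post correlation ρ, the per-arm variance is 2(1 − ρ) for a change score and 1 − ρ² for ANCOVA. At an assumed ρ = 0.5 these are 1.00 and 0.75. Both remove the shared shift; ANCOVA does so more precisely.

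**The case against.** The strongest objections concern the wording and size of the point.

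- **The control group may enter somewhere.** The arms for the paired test are not specified, and the section mentions a regression whose terms are not listed. This is true, but a pooled or arm-by-arm paired test is still not a between-arm test, and no regression with an arm term is stated for F2-isoprostane.
- **No endpoint is labelled primary.** This is also true. F2-isoprostane is still the only oxidative-stress marker given a test of the diet effect.
- **Some shared changes are not built into the design.** This stands in part. Women are not selected on F2-isoprostane, so regression to the mean should be small. Nothing is said about assay batching, so drift is only possible. Abstinence from alcohol may begin at screening, before the pre-diet sample. Supplied food and daily attendance remain, and both are documented.
- **The shared shift is assumed and could be small.** This stands for the size of the problem. At 0.1 SD the false-positive rate is only 6% to 10%. But the protocol gives no reason to expect a negligible shift, and a randomised control group makes that assumption unnecessary.
- **The fix costs power.** This stands. Take an effect that gives the one-arm paired test 80% power with 20 women (0.66 SD of change). With 20 per arm, a between-arm change-score test then has about 53% power and ANCOVA about 65% at ρ = 0.5. The extra paired power comes from assuming that controls do not change.

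The analysis could also be said to belong in a statistical analysis plan. But the protocol names the test, and the named test does not fit the design.

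**Conclusion.** The concern holds and must be fixed. The only stated test of the restriction effect makes no use of the randomised comparison, so the analysis as written does not answer the trial's question. This follows from the text and needs no assumption.

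The size does rest on assumptions. With no true effect and a shared shift of 0.3 to 0.5 SD, between 14% and 87% of trials with 10 to 40 women per arm would show a significant paired change, against a nominal 5%. With a shift near zero the inflation disappears.

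**What to change.** Replace the paired-test sentence in the Statistical analysis section with wording such as:

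> The effect of energy restriction is the between-arm difference (75% versus 100%) in end-of-diet F2-isoprostane, estimated by ANCOVA with randomised arm as the factor and baseline F2-isoprostane as covariate, in all randomised women as assigned, and reported with a 95% CI and p-value. Within-arm changes are descriptive only.

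An arm-by-time term in a repeated-measures model would also cure the defect.

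Two details need settling with it. End-of-diet must be tied to one sample, because the schedule of tests puts the last diet-period blood draw on day 29 while the Blood Analysis table has day 28; these should be reconciled. The handling of missing end-of-diet values should also be stated, there or in the analysis plan.

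No new data are needed, since blood is already scheduled on day 0 and at the end of the diet. The cost is a wider interval and lower power than the one-arm paired change. If the sample size was chosen for the paired test, its adequacy should be rechecked. The section is written in the past tense; if the analysis has already been run, the between-arm result should be reported and the change of method disclosed.

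### The multivariate repeated-measures ANOVA for adiposity would, in its classical form, use only women with complete F2-isoprostane data; a mixed model would keep partial records at wording-only cost

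*Protocol*

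**What the plan says.** The Statistical analysis section of the protocol describes two separate analyses of F2-isoprostane.

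- **Diet effect.** The effect of energy restriction "was evaluated using a paired t-test on the pre- and post-diet measurements", so it uses two values per woman.
- **Adiposity.** The question is put as "The effects of adiposity on F_2_-isoprostane concentration at different time points". The method given for it is that the answer is "determined by a multivariate analysis of variance with repeated measures", and the only explanatory variable named is body fat.

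The section does not say which time points, or how many, enter the second analysis. The Blood Analysis section includes isoprostanes in its assay list ("catecholamines, insulin, leptin, isoprostanes, carnitine, c-reactive protein" and others) but does not assign assays to draws. The Experimental Design section adds to the 28-day diet phase "4 follow up visits (at week 2 and months 3, 6, and 12 after the dietary study", and its chart marks blood at each of those visits.

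**The concern.** A classical multivariate ANOVA treats each woman's repeated values as one outcome vector. If one element is missing, she is removed from the whole test, and the samples she did give are discarded with her.

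Two things are at stake, both for the adiposity analysis only:

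- **Precision.** Samples already collected and assayed go unused.
- **Bias.** An analysis of complete cases is generally unbiased only if missingness is unrelated to the outcome, or depends only on the modelled covariate, here body fat. If women with high or low earlier F2-isoprostane values are more likely to miss later draws, the body-fat slope at later visits can be distorted. A correctly specified likelihood-based mixed model stays valid when missingness depends on values already observed.

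The protocol itself names this method, so the choice is not simply left to a later document. A schedule with repeated draws and visits out to 12 months makes some missed samples plausible.

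**Working it through.** **No figure to reproduce.** The protocol states no sample size, missing rate or dropout rate, so the size of the loss can only be shown over assumed values.

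**Inputs from the protocol**

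- Blood draws in the Experimental Design chart from day 0 to the end of the diet phase: days 0, 3, 5, 7, 14, 21 and 29, which makes 7.
- Follow-up draws: 2 weeks and 3, 6 and 12 months, which makes 4. Total from day 0: 7 + 4 = 11.
- The Blood Analysis table lists a different set: "Days | -7 | 0 | 3 | 5 | 7 | 14 | 21 | 28 | 35", which is 9 draws, plus the same 4 at follow-up, 13 in all. The chart has 12 if the screening draw is counted (1 + 7 + 4). The number of time points therefore cannot be read off the schedule with certainty.

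**Assumptions**

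- A fraction m of samples is missing at each draw, independently within and between women, with m = 3%, 5% or 10%.
- The number of time points k is 3 (an illustrative short list), 7 or 11.

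**Formula.** Share of women with a complete vector = (1 − m)^k.

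| Time points k | m = 3% | m = 5% | m = 10% |
| --- | --- | --- | --- |
| 3 | 0.97^3 = 91% | 0.95^3 = 86% | 0.90^3 = 73% |
| 7 | 0.97^7 = 81% | 0.95^7 = 70% | 0.90^7 = 48% |
| 11 | 0.97^11 = 72% | 0.95^11 = 57% | 0.90^11 = 31% |

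A mixed model uses every observed sample, that is 1 − m of those planned: 97%, 95% and 90%, whatever k is. At m = 5%, the samples obtained but discarded by the complete-case method are, as a share of those planned:

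- k = 3: 0.95 − 0.857 = 9%
- k = 7: 0.95 − 0.698 = 25%
- k = 11: 0.95 − 0.569 = 38%

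**Clustering.** Independence is the unfavourable case. If all missing samples fell in the same women, the complete share would be 1 − m, or 95% at m = 5%, and nothing observed would be discarded. The true loss lies between these two cases.

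**Bias, by illustration.** A simulation with every parameter assumed used 50 women, 8 time points, a true body-fat slope of 0.50, dropout made more likely by a high previous value, and 200 runs. On average 71% of women were complete. The mean slope at the last visit was 0.43 from complete cases and 0.52 from a likelihood fit with unstructured covariance to all observed values (Monte Carlo standard error about 0.012). The complete-case shortfall, 0.50 − 0.43 = 0.07, is about six standard errors; the likelihood fit is within two of the truth. This shows that the bias can occur under such dropout. It does not estimate the bias in this trial.

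**The case against.** **The randomised comparison.** A reader might infer that losing incomplete women breaks the balance of the randomised arms. The protocol does not support this. The model's stated explanatory variable is body fat, which is not randomised, and the sentence makes no arm comparison. The diet effect is tested separately on two measurements, which deletion from this model does not touch.

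**Small trial, many degrees of freedom.** A reader might also infer that an unstructured multivariate test is too costly in a small trial. The protocol gives no sample size, and the number of time points is unstated, so that argument has no footing.

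**Many draws.** It is tempting to assume that all 7 or 11 draws enter. The text says nothing of the kind, and a short list is equally consistent with it. Body composition, for example, is charted up to the end of the diet only at screening 2 and on days 15 and 29. With few time points the loss is modest. This objection stands, which is why the result is given as a range.

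**Attendance.** Women come to the research centre daily for study food, so draws during the diet fall on days when they attend anyway, and missed samples may cluster in a few women. This also stands, and it makes the independent-missingness figures an upper guide.

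**Certain deletion.** The protocol names no command and no missing-data rule. Some univariate repeated-measures routines keep partial records, and imputation could be specified in an analysis plan that is not shown. It cannot be said that women will certainly be dropped. However, the protocol does name the multivariate form, whose classical version works on complete vectors.

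**Conclusion.** The point holds for the adiposity analysis alone, as a minor matter. The protocol names a method that, in its classical form, analyses only complete women and needs a stronger missing-data assumption than the alternative, and it does not name the time points.

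At an assumed, independent 5% missing rate, the share of women retained runs from 86% (3 time points) through 70% (7) to 57% (11), and higher if missed samples cluster. All of this rests on a classical MANOVA without imputation, and on missing rates that the protocol does not give. The test of the diet effect and the randomised comparison are not called into question here. The case for changing is that the better method costs almost nothing.

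**What to change.** In the Statistical analysis section, replace the multivariate repeated-measures ANOVA with a linear mixed model for repeated measures:

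- fitted by REML to every available F2-isoprostane value;
- visit as a factor, with body fat and the body fat-by-visit interaction as fixed effects, so that the question about adiposity at each time point is kept;
- diet arm as a covariate;
- a named covariance structure for the repeated values.

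State which draws enter the model, and report the diet phase separately from the off-diet follow-up.

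The cost is a change of analysis wording. No visit, sample or assay changes, and both software packages named in the protocol can fit the model. The small downside is that it relies on a missing-at-random assumption and on the chosen covariance structure, both of which should be stated. If hardly any samples are missing, little is lost by the change.

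### Terms enter the body-fat/F2-isoprostane model only if P < 0.05 and are then judged at the same 0.05, so what that model reports is distorted by selection

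*Protocol*

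**What the plan says.** The Statistical analysis section describes two analyses of F2-isoprostane. For the diet: "The effect of energy restriction on F_2_-isoprostane was evaluated using a paired t-test on the pre- and post-diet measurements". For adiposity, the effects at different time points are "determined by a multivariate analysis of variance with repeated measures in which body fat was treated as the independent variable".

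It then gives the rule at issue: "A P-value < 0.05 was used for inclusion of terms in the regression and to indicate statistical significance". The section lists no candidate terms, names no selection procedure (forward, backward or univariable screening) and protects no term from the rule. It does not say which analysis the word regression refers to. The body-fat model is the natural referent, because it is the only multivariable model in the document.

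Baseline characteristics are handled separately: "The baseline characteristics between treatment and control groups are compared using the non-parametric Wilcox test". Nothing links the results of those tests to entry into a model.

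**The concern.** A term admitted because it reached P < 0.05, then assessed at P < 0.05 on the same observations, has already passed its own test. The second use of the threshold adds no evidence. Selection also keeps the data sets in which chance made the estimate large and discards those in which it came out small. The average of what is reported therefore lies further from zero than the truth, and the printed P-value and interval take no account of the selection.

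The adiposity estimate is what is at stake. The diet could change both body fat and F2-isoprostane during the study. Whether the body-fat effect is adjusted for arm, or for anything else, should then be a design decision. Under this rule it depends on whether the other term happens to cross 0.05. If body fat itself is subject to the rule, and nothing exempts it, a result that misses 0.05 may leave no estimate at all.

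**Working it through.** **What the protocol supplies.** One number, the 0.05 threshold for both entry and significance. It states no sample size, SD, effect size, correlation or candidate list, so there is no figure of the plan to reproduce. Everything below is an illustration on assumed inputs.

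**Step 1: why selection inflates.** Take a two-level term with n women per level, residual SD 1 and true effect d in SD units. The estimate has standard error √(2/n), and the term is kept only if the estimate exceeds about t × √(2/n) in absolute value.

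- n = 20: √(2/20) = 0.316 and t(38 df) = 2.024, so the bar is about 0.64 SD. If d = 0.5, a kept estimate in the right direction is typically at least 0.64/0.5 = 1.28 times the truth.
- n = 40: √(2/40) = 0.224 and t(78 df) = 1.991, so the bar is about 0.45 SD. If d = 0.8, the bar lies well below the truth and little is cut off.

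**Step 2: simulated size.** Ordinary least squares, 4000 runs per row, term kept only if two-sided P < 0.05:

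| n per level | True effect (SD) | Kept | Mean estimate when kept ÷ true effect | 95% CI coverage when kept |
| --- | --- | --- | --- | --- |
| 10 | 0.3 | 9% | 3.13 | 0.70 |
| 10 | 0.5 | 18% | 2.21 | 0.86 |
| 10 | 0.8 | 39% | 1.51 | 0.92 |
| 20 | 0.3 | 15% | 2.49 | 0.82 |
| 20 | 0.5 | 34% | 1.68 | 0.92 |
| 20 | 0.8 | 69% | 1.20 | 0.96 |
| 40 | 0.3 | 27% | 1.91 | 0.91 |
| 40 | 0.5 | 60% | 1.28 | 0.96 |
| 40 | 0.8 | 94% | 1.03 | 0.97 |

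The two-level term stands in for any candidate term. Body fat is continuous and the protocol's model has repeated measures, so the mechanism carries over but the exact multiples do not.

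**Step 3: noise terms entering.** With k independent null candidates, the chance that at least one passes is 1 − 0.95^k:

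- k = 3: 1 − 0.857 = 14%
- k = 5: 1 − 0.774 = 23%
- k = 10: 1 − 0.599 = 40%

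**Step 4: genuine adjustment terms left out.** A covariate truly correlated with the outcome fails P < 0.05, and is dropped, in these shares of simulated trials (4000 runs each):

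| Total N | Correlation 0.3 | Correlation 0.5 | Correlation 0.7 |
| --- | --- | --- | --- |
| 20 | 75% | 39% | 6% |
| 40 | 54% | 8% | 0.1% |
| 80 | 23% | 0.3% | 0% |

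This shows how far adjustment can depend on chance. It does not imply that the protocol plans any particular covariate.

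**Step 5: false-positive rate of a null term.** Under backward elimination at 0.05 with 3 to 8 other null terms (total N 20 or 40, 3000 runs each), a null term was kept in 5.6% to 8.5% of runs. With the model fixed in advance it was significant in 4.7% to 6.1%, which is nominal or close to it. The worst case was 8.5% against 5.3%, at N = 20 with 8 other terms.

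**The case against.** The strongest reply is that the rule leaves the trial's main question alone. That is right. A reader might infer that an arm effect missing 0.05 would be dropped and not estimated, that a positive diet effect would be exaggerated, or that baseline F2-isoprostane could fall out of the treatment comparison. The documents do not support any of these. The diet effect is assigned to a paired t-test, which gives an estimate whatever its P-value, and neither arm nor baseline F2-isoprostane is named as a term or candidate in any model. That no term is protected does not show that these two are candidates. The protocol does describe two randomised groups ("We will conduct a randomized trial in women assign to one of two groups"), and whether its pre/post test uses that randomisation is a separate question which this rule neither creates nor cures.

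It can also be said that a list of model terms is commonly left to the SAP. That holds for the list, but the protocol itself states the selection rule, and the rule is what is wrong.

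Third, every multiple above rests on invented inputs, and the effect nearly vanishes at 40 per arm with an effect of 0.8 SD. That also stands, and no single figure should be quoted as the bias in this trial.

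Last, inflation of the false-positive rate for a given null term is modest. It was about 5.1% in a forward-selection simulation (40 women, six noise terms) and at most 8.5% under backward elimination. The main harm is to estimates, intervals and the choice of adjustment. None of these replies rescues the rule within the body-fat model.

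**Conclusion.** The concern holds for the adiposity/F2-isoprostane model only. There the stated rule makes retained terms significant at entry, overstates their effects, invalidates their nominal P-values and intervals, and leaves adjustment of the body-fat effect partly to chance. The paired t-test of the diet effect is unaffected.

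The direction of the bias follows from the rule, but its size cannot be derived from the protocol. On the assumed inputs, overstatement of a retained term runs from about 3.1 times (0.3 SD, 10 per arm) to 1.03 times (0.8 SD, 40 per arm), and at least one of 3 to 10 independent null candidates enters in 14% to 40% of trials. This assumes that the word regression refers to the body-fat model, the only multivariable model described.

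**What to change.** In the Statistical analysis section, delete the part of the sentence that makes 0.05 a criterion for entering terms, and keep 0.05 only as the significance level. Add that the terms of the body-fat model are fixed in advance (body fat and time, with randomised arm as an adjustment term), stay in whatever their P-values, and are reported with 95% CIs.

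The cost is a short edit and a few degrees of freedom for the fixed terms. No assumed sample size or effect size is needed. The change leaves the paired t-test as it is and does not supply a between-arm comparison.
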